### Randomisation and allocation concealment

Patients will be randomly assigned to either of the two exercise groups with a 1:1 allocation as per a computer-generated randomisation schedule, stratified by administration of concomitant corticosteroid injection using permuted blocks of random sizes (two to six). The primary investigator, assessors and administrator of the randomisation procedure will not know block sizes in order to ensure allocation concealment. In practice, after recruitment and baseline measurements, the secretary at the physiotherapy department will administer the allocation procedure by taking a sequentially numbered, opaque sealed envelope from one of two ring binders, determined by the potential referral to corticosteroids (yes or no) by the orthopaedic specialist.

### Blinding

Outcome assessors will perform both baseline and follow-up assessments, and will be kept blinded from treatment allocation. At the follow-up assessments, patients will be strongly encouraged not to disclose the components of their exercise programme, in order to keep the outcome assessor blinded. Patients will be blinded regarding exercise allocation by informing them that the trial involves testing two exercise programmes consisting of the same exercises, and that they will be performed in two different ways, but not defining the specific difference between these, or which is hypothesised to be more effective.

### Statistical analysis plan

The primary efficacy analysis performed is assessment of the between-group difference in change in the DASH score after 12 weeks in the intent-to-treat (ITT) population (all randomised patients independent of compliance and withdrawals). In the case of missing data due to drop-outs, a non-responder imputation will be applied; a baseline observation carried forward (BOCF) technique will be used for patients who do not complete the study (as will be illustrated in a corresponding trial flow diagram).

For the primary analyses at week 12, we will use analysis of covariance (ANCOVA) to compare the progressive high-load exercise group with the low-load exercise group for mean changes from baseline in the DASH score, as well as the secondary continuous outcomes. The primary model includes the change from baseline as the dependent variable, with treatment group (progressive high-load exercise or low-load exercise), corticosteroid status (yes or no), and the centre site (one, two or three) as main effects, with the baseline score as an additional covariate. The secondary analysis for the primary outcome will add the interaction term for group × corticosteroid in the primary model.

To analyse the longitudinal element of time effects of DASH in the randomised trial (repeated measures design three, six, nine, and 12 weeks), a linear approach will be used, fitted in SAS software (version 9.3 Service Pack 4; SAS Institute Inc., Cary, North Carolina, United States) using the procedure ‘PROC MIXED’ based on restricted maximum likelihood (REML) estimates of the parameters. The variable ‘patient’ will be applied as a random effects factor. Assessment of the treatment and time effects is of exploratory interest for the primary outcome in testing for a possible interaction, and both treatment and time will be used as systematic factors, using the baseline value as covariate to reduce random variation and increase power.

For all of the above analyses, results will be expressed as the difference between the group means and 95% confidence intervals with associated *P* values, based on the mixed linear model. All data analyses will be carried out according to the pre-established analysis plan, and will be performed applying SAS software. All descriptive statistics and tests will be reported in accordance with the recommendations of the Enhancing the QUAlity and Transparency Of health Research (EQUATOR) network [48] and the Consolidating Standards of Reporting Trials (CONSORT) statement [49]. In order to evaluate the empirical distributions of the continuous outcomes, visual inspection (of the studentised residuals from the statistical model) will be used to suggest whether the assumption of normality and variance homogeneity is reasonable.

Statistical analysis of the economic variables will be presented as descriptive statistics, and a cost-utility analysis of the economic burden of each specific exercise programme in relation to the EQ-5D will be performed, expressed in quality-adjusted life years (QALYs) gained.

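### The results sentence credits every analysis to the mixed linear model, which blurs the source of the primary ANCOVA estimate, and the exploratory repeated-measures model is more restrictive than it need be

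*Protocol article*

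**What the plan says.** All the relevant text is in the Statistical analysis plan section of the protocol article.

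- **Primary analysis.** "For the primary analyses at week 12, we will use analysis of covariance (ANCOVA"). Besides treatment group, the primary model contains "corticosteroid status (yes or no), and the centre site (one, two or three) as main effects, with the baseline score as an additional covariate". Patients who do not complete the study have their baseline value carried forward (BOCF).
- **Repeated-measures analysis.** DASH at weeks 3, 6, 9 and 12 is to be fitted in PROC MIXED by REML. On the random part: "The variable ‘patient’ will be applied as a random effects factor". On the fixed part: "both treatment and time will be used as systematic factors, using the baseline value as covariate to reduce random variation and increase power". Neither corticosteroid status nor centre is listed. Its status is given too: "Assessment of the treatment and time effects is of exploratory interest for the primary outcome in testing for a possible interaction".
- **Reporting.** "For all of the above analyses, results will be expressed as the difference between the group means and 95% confidence intervals", with P values, "based on the mixed linear model".

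The section Randomisation and allocation concealment names corticosteroid injection as the only stratification factor.

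**The concern.** Two things look wrong.

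First, the reporting sentence covers every analysis above it, and so includes the ANCOVA, yet it names the mixed linear model as the source of the estimates. The only mixed model described is the exploratory one. The ANCOVA as written has no random term. Someone writing the analysis code from this text could take the headline difference from either model, and the two need not agree when patients drop out.

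Second, the mixed model does not match the primary model one paragraph earlier, because it drops the stratum and centre. With a random patient effect and no other stated structure, it imposes one variance at all four visits and one correlation between every pair of visits. The model exists to examine the treatment-by-time pattern, and that is the comparison most sensitive to a wrong correlation structure.

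**Working it through.** **The plan's own figure.** A two-sided t-test at 0.05 with 100 per group, difference 10 and SD 17 has power 0.9853, against 0.985 stated. It reproduces, and nothing below alters it.

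**1. ANCOVA with BOCF against a mixed model on observed visits.** The expected changes are 20 points (high-load) and 10 points (low-load), from Sample size and power considerations. The drop-out rates are assumptions, with drop-out unrelated to outcome. BOCF sets a drop-out's change to 0, so the expected difference is (1 − d₁) × 20 − (1 − d₂) × 10.

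| Drop-out, high-load / low-load | BOCF difference |
|---|---|
| 15% / 15% | 17.0 − 8.5 = 8.5 |
| 20% / 10% | 16.0 − 9.0 = 7.0 |
| 10% / 20% | 18.0 − 8.0 = 10.0 |

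A REML model on the observed visits targets about 10 in each row. The gap would close if BOCF-filled data were fed to the mixed model. The article does not say that they would be.

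**2. Leaving out the stratum.** Assume 130 per arm, a balanced stratum at a 50% split, and a baseline correlation of 0.5, so the residual variance is 17² × 0.75 = 216.75 (SD 14.7). A stratum effect of s points left in the residual adds s² × 0.25. For a week-12 comparison, SE = √(2 × variance / 130).

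- s = 0, or the term included: √(2 × 216.75 / 130) = 1.83
- s = 5: √(2 × 223.0 / 130) = 1.85
- s = 10: √(2 × 241.75 / 130) = 1.93

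In simulation (4000 runs) the estimate is unbiased. Type I error without the term is 4.8%, 4.8% and 3.4% for s = 0, 5 and 10. At a true difference of 5 points with s = 10, power is 75% without the term and 79% with it. At 10 points it is about 100% either way. The plan hypothesises a 10-point corticosteroid effect only within the high-load arm. If the low-load effect were zero (an assumption), the average would be 5 points, so s = 10 is a generous case.

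**3. Random patient effect only, treatment-by-time contrast.** Assume equal variances and a true AR(1) correlation ρ between adjacent visits. A random-intercept fit uses roughly the average pairwise correlation, r = (3ρ + 2ρ² + ρ³)/6. The true correlation between weeks 3 and 12 is ρ³. The model SE of the week-12 minus week-3 treatment contrast, relative to its true value, is √[(1 − r)/(1 − ρ³)]. The type I error is 2 × [1 − Φ(1.96 × ratio)].

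| ρ | r | 1 − ρ³ | SE ratio | Type I error |
|---|---|---|---|---|
| 0.9 | 0.842 | 0.271 | 0.765 | 13% |
| 0.8 | 0.699 | 0.488 | 0.786 | 12% |
| 0.7 | 0.571 | 0.657 | 0.809 | 11% |

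So the SE is 19 to 24% too small. Simulation of the omnibus treatment-by-time test under the same assumptions gives a type I error of about 6 to 7%.

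**4. Random patient effect only, week-12 difference.** With equal variances the week-12 SE is unchanged whatever ρ is: √(2 × 17² / 130) = 2.11 under either structure. It changes only if residual variance grows over time. As an illustration, assume baseline correlations of 0.8, 0.7, 0.6 and 0.5 at the four visits. Residual SDs are then 17√(1 − correlation²) = 10.2, 12.1, 13.6 and 14.7, and their root mean square is 12.8. The ratio 12.78/14.72 = 0.868 makes the week-12 SE 13% too small, and nominal 5% becomes 2 × [1 − Φ(1.96 × 0.868)] = 8.9%. With constant variance and correlation there is no error.

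**The case against.** The strongest reply is that the primary analysis is not in doubt. The text says "we will use analysis of covariance (ANCOVA) to compare the progressive high-load exercise group with the low-load exercise group", lists the terms of that model, and labels the PROC MIXED analysis exploratory. An ANCOVA is a linear model and can be run in PROC MIXED, so the closing phrase may be no more than loose wording. This stands. A reader might infer that the protocol sets up two rival primary analyses. It does not, because a trailing phrase about reporting does not override an explicit designation. What remains is that the phrase points to the wrong model and should be corrected.

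The stratum is already in the primary model, and omitting it from the exploratory one causes no bias and errs on the cautious side. Centre is not a stratification factor, so its absence does not depart from the randomisation. Both points stand.

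A reader might also infer that the week-12 standard errors are understated. The documents give no between-visit correlations, so that cannot be asserted. It follows only if residual variance rises after baseline adjustment, and then only for the exploratory estimate.

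Finally, covariance structure is often left to a fuller analysis plan, and the article refers to one that is not shown. That lowers the weight of the point. It does not remove it, because the article states a random part and a set of fixed terms, and as stated these are weaker than an alternative that costs almost nothing.

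**Conclusion.** The point holds in a limited form. The reporting sentence blurs which model produces the primary estimate. This has consequences only with drop-out: 8.5 against about 10 points at an assumed 15% per arm, and from 7 to 10 points under BOCF for the unequal rates tried.

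The exploratory model loses a little precision by leaving out the stratum (SE 1.93 against 1.83 at most in the cases tried). If correlation fades with time, as in the assumed AR(1) range of 0.7 to 0.9, its treatment-by-time test is mildly anticonservative: about 6 to 7% overall, and 11 to 13% for the week-12 versus week-3 contrast. Under constant variance and correlation that test has no such error. The primary ANCOVA, which uses week-12 data alone and includes stratum and centre, is unaffected, as are the sample-size figures.

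**What to change.** 1. Reword the reporting sentence so that the primary difference, confidence interval and P value come from the week-12 ANCOVA, and the repeated-measures results are reported as exploratory. State whether the mixed model uses observed visits only or BOCF-filled data.
2. Fit the repeated-measures model with treatment × week, baseline × week, corticosteroid stratum and centre. Centre is included to match the primary model, not because randomisation requires it. Use an unstructured within-patient covariance under REML.

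The cost is one sentence, a few lines of SAS and a few more covariance parameters. A four-visit unstructured matrix has 4 × 5 / 2 = 10 parameters against 2 for a random intercept with residual error, which the planned 260 patients support easily.

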### Interim analysis and early stopping rules

An early stopping rule will be applied when complete rotator cuff ruptures, verified by ultrasonography, occur due to the performance of the exercise programme. If six or more cases of complete rupture occur in the progressive high-load exercise group, and the rate of rupture is 50% more compared with the low-load exercise group, the trial will be stopped.

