### Participants

The orthopaedic specialists will perform a standardized initial screening of all patients referred to the shoulder units. If patients fulfil the eligibility criteria they will be referred to the principal investigator, who will perform the final eligibility assessment and give detailed information about the study. Patients will be invited to participate if they meet the following inclusion criteria: between 18 and 65 years of age, have a current shoulder complaint lasting at least three months prior to the time of enrolment, pain is located in the proximal lateral aspect of the upper arm (C5 dermatome) that is aggravated by abduction, a positive ‘Full Can Test’ and/or Jobe’s test and/or Resisted External Rotation Test, a positive Hawkins-Kennedy test and/or Neer’s test, ultrasonographic verification of either tendon swelling, and/or presence of hypoechoic areas, calcification, fibrillar disruption and/or neovascularisation in the m. supraspinatus.

Patients will be excluded if they fulfil any of the following exclusion criteria: Resting pain more than 40 mm on a visual analogue pain scale (range: 0 to 100), bilateral shoulder pain, less than 90 degrees of active elevation of the arm, a full thickness rupture in the rotator cuff tendon verified by ultrasonography, presence of calcification larger than 5 mm (vertical distance) verified by x-ray, corticosteroid injection within the last six weeks, a radiologically verified fracture, glenohumeral osteoarthritis, prior surgery or dislocation of the affected shoulder, a clinically suspected labrum lesion, symptomatic arthritis in the acromioclavicular joint, a frozen shoulder or symptoms derived from the cervical spine, sensory or motor deficit in the neck or arm, suspected competing diagnoses (for example, rheumatoid arthritis, cancer, neurological disorders, fibromyalgia, psychiatric illness), pregnancy or inability to understand spoken and written Danish.

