### Interventions

Generally, both groups will receive the same exercises (although they differ on the amount of load), attention and basic information about ergonomic corrections related to the daily use of the upper extremity. The exercise program will consist of six exercises: two exercises for the scapula stabilising muscles (push-up plus exercise and low row exercise), two for the rotator cuff muscles (scaption and side-lying external rotation), and two stretching and mobility exercises (posterior capsule stretch and scapulae retraction). Patients will be instructed in performing home-based training three times per week, and will be seen for initial instruction in week one (60 minutes), and follow-up exercise sessions (30 minutes) in weeks two, three, four, six and nine. The general information about the project and exercise instructions will be given through a DVD to minimise the influence of the physiotherapist. On the first visit to the physiotherapist, the patients will receive detailed instructions on how to perform the exercise programme based on the instructions on the DVD. At the follow-up exercise sessions corrections will be made, and weights adjusted. The patients will be given a copy of the DVD and an exercise brochure to enable them to follow the instructions and exercises at home.

The difference between the intervention and control groups will be the external load targeting exercises for the rotator cuff. The intervention group will perform 12 weeks of progressive high-load exercises, gradually increasing the load from 15 repetitions maximum (RM) in week one to six RM in weeks nine to 12. The intervention group will only be allowed to do isometric exercises if the pain exceeds 50 mm on the visual analogue scale. The control group will perform 12 weeks of low-load exercises, performed with 20 RM from weeks one to 12. For both groups, scapulae exercises will be performed with 20 RM, and stretching and mobility exercises will be performed five times, for 20 seconds each, in weeks one to 12.

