### Data monitoring

Since adverse events are expected to be minimal and the intervention is not considered a high-risk intervention, no data monitoring committee will be established. The physiotherapists at each centre will be asked to report adverse events to the primary investigator, who will report these to the ethics committee and monitor if the number of adverse events has reached the threshold for the early stopping rule.

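### The rupture stopping rule appears to filter cases by presumed cause before comparing randomised arms, and its two sentences may define different events

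*Protocol article*

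**What the plan says.** The section on interim analysis and early stopping rules in the Protocol article has two sentences. The first says when the rule comes into play: "An early stopping rule will be applied when complete rotator cuff ruptures, verified by ultrasonography, occur due to the performance of the exercise programme". The second gives the test, in two parts. One part is an absolute count: "If six or more cases of complete rupture occur in the progressive high-load exercise group". The other part is a comparison between the arms, which must also be met: "the rate of rupture is 50% more compared with the low-load exercise group, the trial will be stopped". The second sentence does not repeat the causal condition of the first.

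The Data monitoring section says that "no data monitoring committee will be established". It gives one reporting chain: "The physiotherapists at each centre will be asked to report adverse events to the primary investigator", who passes the events to the ethics committee and will "monitor if the number of adverse events has reached the threshold for the early stopping rule". Neither section says who decides whether a rupture was caused by the exercises, or by what criteria.

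The Study design and Blinding sections describe patients and outcome assessors as blinded, and nobody else. The Interventions section says that the arms differ in the external load on the rotator cuff exercises. Of the physiotherapist-led sessions it says: "At the follow-up exercise sessions corrections will be made, and weights adjusted".

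**The concern.** A rule that compares rupture rates between randomised arms already has its control for natural course, namely the low-load arm. Screening each case for cause before the comparison adds nothing that the comparison needs, and it makes the count depend on an opinion.

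That opinion is hard to form here. Every participant enters with ultrasound-verified supraspinatus changes (Participants), and between 25% and 50% are expected to receive a corticosteroid injection just before randomisation (Interventions). Ultrasonography can establish that a tendon has ruptured completely. It cannot establish why.

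Two things are at stake. The absolute threshold of six is fixed, so removing cases makes it harder to reach, even when cases are removed evenly from both arms. If cases are removed unevenly, the between-arm ratio no longer reflects the randomised comparison. Because there is no independent committee, the wording of the rule carries more weight than it otherwise would.

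**Working it through.** **Stated figures.** The article gives no expected rupture rate and no operating characteristics for the rule, so there is no figure to reproduce. The steps below are illustrations.

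**Step 1: the two sentences side by side.**
- Sentence one: ruptures that are complete, verified by ultrasonography and caused by the programme.
- Sentence two: complete ruptures, with no mention of cause.
- If sentence one governs, there is a case-level causal filter. If sentence two stands alone, all complete ruptures count. The text does not settle which, although carrying the condition forward is the natural reading.

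**Step 2: whether the filter can change the answer on the rule's own thresholds** (equal arm sizes, hypothetical counts).
- Six ruptures in each arm: ratio 6/6 = 1.0, no stop. If all six high-load cases but only four low-load cases are attributed, 6/4 = 1.5 and the rule is met.
- Eight v two: ratio 8/2 = 4, stop. If three high-load cases are not attributed, 8 − 3 = 5, which is below six, and the rule is not met.

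**Step 3: how often.**

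Inputs:
- n = 130 per arm (Sample size and power considerations).
- Stop if X_H ≥ 6 and X_H ≥ 1.5 × X_L (stopping-rule section, with 50% more read as at least 1.5 times).
- One look with all patients observed (assumption).
- True rupture rates p_H and p_L, and attributed shares a_H and a_L (assumptions).

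Counted cases are X_H ~ Binomial(130, p_H·a_H) and X_L ~ Binomial(130, p_L·a_L), taken as independent, so

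P(stop) = Σ from i = 6 to 130 of P(X_H = i) × P(X_L ≤ ⌊i/1.5⌋).

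| True rates, high v low | All ruptures count | Half attributed in each arm |
|---|---|---|
| 8% v 2% | 0.93 | 0.42 |
| 8% v 4% | 0.73 | 0.38 |
| 5% v 2% | 0.59 | 0.11 |

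In the 8% v 2% case the expected high-load count is 130 × 0.08 = 10.4 when all ruptures count, and 10.4 × 0.5 = 5.2 when half do, which is below the threshold. The probability of six or more high-load cases alone is 0.95 under Binomial(130, 0.08) and 0.42 under Binomial(130, 0.04). The loss therefore comes almost wholly from the fixed count of six, since equal filtering leaves the expected ratio unchanged.

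Unequal filtering, with equal true rates of 5%:

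| Attributed share, high v low | P(stop) |
|---|---|
| 100% v 100% | 0.23 |
| 75% v 25% | 0.36 |
| 50% v 100% | 0.03 |

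So unequal attribution can raise or lower the chance of stopping when the arms do not differ at all.

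**The case against.** The strongest reply is that the operative test has no filter. The second sentence speaks of ruptures and a rupture rate without mentioning cause, and the Data monitoring section describes a count against a threshold. That is a possible reading. It does not remove the point, because the first sentence states when the rule applies; if all ruptures were meant, the two sentences need reconciling.

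A reader might go further and infer that unblinded physiotherapists and the primary investigator decide which ruptures count. The documents do not say so. They assign causality assessment to no one, and a condensed article may leave that procedure to the full protocol. What can be said is limited: the only reporting chain given runs through physiotherapists who adjust the loads and then the primary investigator, and neither is described as blinded. The primary investigator's role in confirming eligibility has no bearing on attributing ruptures.

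The direction of any bias is also unsupported. Nothing in the article shows that staff would over-attribute ruptures to heavy loads or discount them as existing disease.

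Some safeguards deserve credit. Each rupture must be confirmed by ultrasonography. A full-thickness rupture is an exclusion criterion, so a later one cannot simply be dismissed as present at entry. Follow-up assessments are made by blinded assessors. These protect the finding of a rupture but not its attribution.

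Finally, simply counting every rupture after randomisation would be open-ended. Follow-up runs to one year, exercise ends at week 12, and Table 1 schedules ultrasonography only at baseline and week 12. Later cases would depend on who happened to be scanned. This objection stands, and the fix needs a defined window.

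**Conclusion.** The point holds in a limited form. On its natural reading the rule selects cases by presumed cause before comparing arms that randomisation already makes comparable. On the other reading, its two sentences define different events. Either way the event definition needs correcting.

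The size is illustrative. With 130 per arm, one look and assumed rates of 8% v 2%, attributing half the cases in each arm cuts the chance of stopping from 0.93 to 0.42. With equal assumed rates of 5%, unequal attribution moves it between 0.03 and 0.36, against 0.23 when all ruptures count. The rupture rates and attributed shares are assumptions, and the article expects adverse events to be minimal, so true rates may be far lower.

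It would be too strong to conclude that the rule will give a wrong answer or that unblinded opinion decides it. That would require attribution to be applied and to remove a material share of cases, and the article establishes neither. The rule does not enter the primary efficacy analysis.

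**What to change.** Reconcile the two sentences of the stopping-rule section by deleting the causal qualifier that ends the first. State that every ultrasound-verified complete rupture counts, by randomised arm, over one stated window that is the same in both arms. Randomisation to the week 12 assessment is one example, since ultrasonography is already scheduled there for all patients. Report presumed cause as a descriptive item only. Leave the count of six and the 50% margin as they are; this point takes no view on them.

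The cost is a change of wording plus a stated window, with no additional scans if the window ends at week 12. The downside is that a few ruptures with an obvious other cause, such as a fall, will be counted. Randomisation should spread these similarly over the two arms.
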